### Study Objective

The primary objective of this study is to examine the impact of ABF on acute care hospitals and related services in B.C. This objective will be fulfilled by meeting two specific aims.

**Aim 1**: To measure internal (to the hospital) changes resulting from the shift toward ABF. In a longitudinal analysis of observational data, we will measure whether and how hospitals respond to the changed financial incentives. Related hypotheses include:

**Hypothesis 1.1**: Lengths of stay will decrease and case mix adjusted volume of patients will increase from baseline levels. We will test for changes in trend over time.

**Hypothesis 1.2**: There will be changes in in-hospital quality measures (mortality and adverse events) for specific conditions that are characterized by their variability in clinical utilization patterns. We will test for changes in trend over time.

**Hypothesis 1.3**: Hospitals' expenditures will increase from baseline levels. We will construct a model to detect changes in trend over time of hospital expenditures.

**Aim 2**: To measure external (to the hospital) changes. In a longitudinal analysis of observational data, we will measure whether other components of the health care system are affected by the shift toward ABF. Related hypotheses include:

**Hypothesis 2.1**: There will be an increase in 30 day readmission rate, rate of admissions from emergency department (ED) and rate of admissions for ambulatory sensitive conditions, all indicators of sub-optimal acute care. We will test for an increase in the rates over time.

**Hypothesis 2.2**: There will be an increase in the number of new home care patients subsequent to being discharged from acute care. We will construct a model to detect changes in the trend of: 1) new home care patients over time and 2) readmissions to acute care from home care over time.

**Hypothesis 2.3**: There will be an increase in expenditures on physician services. We will test for an increase in physician expenditures over time.

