## Methods/Design

### Design

This study has been approved by the University of British Columbia's Research Ethics Board.

#### Aim 1

We do not expect ABF to affect all patient types uniformly. Conditions for which patterns of care are well defined are expected to be invariant to hospital funding incentives. Accordingly, we will map all hospitalizations into one of three 3 care types; *supply sensitive care, preference sensitive care *and *evidence-based care*. The rationale for stratifying analyses into these 3 categories is that utilization intensity has been shown to vary by condition, region and clinician preference [24]. For each stratum, the change in the average length of stay and number of discharges is expected to vary (as shown in the 2^nd ^column of Table 1).

**Table 1 T1:** Expected response of hospitals to ABF by type of care provided

Care Type	Expected Response	Reason for Hospitalization
**Supply Sensitive**	Some Response	Congestive heart failure
		Cancer
		Chronic lung disease
	
**Preference Sensitive**	Unknown	Benign prostatic hypertrophy
		Hip replacement
		Knee replacement
	
**Evidence-based Care**	None	Appendectomy
		Leg fracture

In addition to overall case mix adjusted volume and day surgery volume, we will calculate average lengths of stay for case mix adjusted volume of patients for each condition listed in the third column of Table 1. We will use ICD-10-CA codes underlying the CMG; a strategy for identifying hospitalizations that ensures that the conditions identified in Table 1 are the primary reason for hospitalization (and removes patients whose hospitalization is for reasons other than those listed).

In-hospital quality and outcomes as a result of a shift to ABF will be monitored in B.C. and shared with the MoHS. Based on broadly accepted in-hospital quality indicators [25], our hospital quality indicators will be mortality rates for selected medical and surgical patients (shown in Table 2), overall mortality rates plus the number of patient safety and adverse events [26].

**Table 2 T2:** Conditions for calculating age, sex and risk adjusted in-hospital mortality rates

Type	Title	Method for Identifying Cases
**Medical**	Acute myocardial infarction	ICD-10-CA codes
	Congestive heart failure	
	Stroke	
	Gastrointestinal hemorrhage	
	Pneumonia	
	
**Surgical**	Esophageal resection	CCI codes
	Pancreatic resection	
	Carotid endarterectomy	
	Craniotomy	
	Hip replacement	

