Hospital mortality rates will be calculated as the number of inpatient deaths relative to the number of separations for the conditions listed in Table 2. Methods for calculating mortality rates for surgical patients are based on the Leapfrog Group's evidence-based hospital referral (EBHR) standards for surgery, while mortality rates for medical conditions are based on low mortality patient groups [27] for which mortality is an unexpected outcome. We will adjust hospital mortality rates for differences between hospitals of age, sex and risk profiles of patients [28,29].

We will also calculate in-hospital event rates, representing unintended injuries or complications of care [30] per volume of surgical separations and analyze changes in trend over time. These rates include: *post operative sepsis (surgical site infection); post operative thrombo-embolism; *and *repeat trips to the OR*. These quality indicators are commonly applied and can be readily computed with B.C.'s hospital separation data.

Finally, we will adjust hospital expenditure data to control for factors associated with price inflation over time, such as labour contract increases, in order to isolate ABF-related changes in expenditures.

#### Aim 2

Since all segments of the health care system are intertwined, even if funding streams are not, this study provides a first-ever opportunity to develop knowledge regarding the non-hospital consequences of ABF. To examine health system effects, we will calculate three categories of indicators: *early discharge from hospital *(resulting in readmission to hospital); *access to care; *and (inappropriate) *admissions for ambulatory care sensitive conditions *(see Table 3).

**Table 3 T3:** Indicators of early discharge, access and admissions for ambulatory care sensitive conditions

Impact	Condition	Level of Reporting
**Readmission**	All Cause	Hospital
	Acute myocardial infarction	Hospital
	Prostatectomy	Hospital
	
**Access**	Emergency department admission rate Hip fracture surgery within 2 days of admission	Hospital
	Hip fracture surgery within 2 days of admission	Hospital
	
**Ambulatory care sensitive conditions**	Dehydration: hospital admission rate	Health Authority
	Diabetes mellitus: hospital admission rate	Health Authority

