### Analysis

Initially, we will provide descriptive analyses of the overall trend in provincial LOS and case mix adjusted volume. We will then construct a multivariate zero-truncated Poisson regression model to identify factors associated with length of stay for each condition included in Table 1. The dependent variable, length of stay of patient *i*, is *Y*_*i*_. The regression model effects include: hospital and patient level effects, ***X***_***i***_, (such as age and ACG). Hospital level clustering will be incorporated into the model. The model is:

where time and policy (and interaction between time and policy) represent study month (1,2,3...) and an indicator variable for ABF, respectively.

If the MoHS changes ABF policy during the study period (e.g., to 30% of acute funding), we will change the parameterization of the model to reflect the change. The parameters of interest are θ and τ, where θ represents an immediate change in the length of stay and τ represents a change in the trend in length of stay. The results will be presented as absolute and relative changes to facilitate interpretation. While we are confident these methods are appropriate for the data and the questions being addressed, if small sample sizes inhibit analysis, we will explore composite measures (which combine multiple conditions) for standardized rates [36-38].

We will use a linear regression model to examine the relationship between ABF and hospitals' case mix adjusted volume of cases (transformed for normality if needed). The dependent variable, *Y*_*i*_, is the hospital's monthly number of case mix adjusted cases. Repeated measures (clustering) on hospitals over time will be incorporated into the model through ***X***_***i***_, a vector of hospital effects. The regression equation is written:

where the parameters of interest are change in level (θ) and change in trend (τ). We will construct a regression model for overall weighted cases plus a separate regression model for each condition included in Table 1.

We will model the number of in-hospital medical and surgical deaths, *Y*_*i*_, (as described in Table 2) relative to the total number of separations, *N*_*i*_, using a Poisson model for count data. The vector ***X***_***i ***_will include hospital effects and adjust for repeated measurements on the same hospital. The regression model is written:

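### Mortality counted only up to discharge can fall, or hide harm, if ABF shortens stays as the study predicts; the promised risk adjustment is also not carried into the described mortality model

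*Protocol article*

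**What the plan says.** **Outcome.** The Design section (Aim 1) defines the measure, for the Table 2 conditions: "Hospital mortality rates will be calculated as the number of inpatient deaths relative to the number of separations". The Analysis section repeats it in model form: "We will model the number of in-hospital medical and surgical deaths", taken "relative to the total number of separations", in a Poisson model. The parameters of interest are an immediate change and a change in trend after ABF.

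**Predicted effect of the policy.** Hypothesis 1.1 (Study Objective) reads: "Lengths of stay will decrease and case mix adjusted volume of patients will increase from baseline levels". The Background section on the information base for ABF explains why: case payment is largely independent of length of stay, so hospitals gain by discharging earlier.

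**Risk adjustment.** The title of Table 2 is "Conditions for calculating age, sex and risk adjusted in-hospital mortality rates". The Design text adds: "We will adjust hospital mortality rates for differences between hospitals of age, sex and risk profiles of patients". In the Analysis section, the covariate vector of the mortality model will "include hospital effects and adjust for repeated measurements on the same hospital"; no patient characteristic is named there. The length-of-stay model and the physician-expenditure model, by contrast, do name patient-level covariates.

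**Data.** The Aim 1 dataset is to hold an indicator of death and Adjusted Clinical Groups (ACG), and hospital records are to be linked to the registry. The article does not state whether the death indicator covers deaths after discharge.

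**The concern.** Two separate problems bear on the same test.

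1. *Truncation at discharge.* The outcome is observed only while the patient is in hospital, and the policy is expected to shorten that time. Part of any post-ABF fall in deaths per separation may then reflect a shorter observation period. A true rise in mortality can be offset in the same way. Risk adjustment does not repair this, because the same patient with the same risk is simply watched for less time.

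2. *Adjustment over time.* Hospital effects already absorb stable differences between hospitals. With no control group (Study Limitations), what threatens a before/after comparison is a change in patient risk within hospitals. The promised adjustment is worded for differences between hospitals, and the model text does not mention patient risk.

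The Discussion asks whether efficiency is gained without loss of quality, and the Design section says that results will be shared with the ministry. A misleading mortality result would therefore go straight to the decision-maker.

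**Working it through.** The article gives no mortality rate, mean stay, expected reduction in stay or power for this outcome, so there is no figure to reproduce. All inputs below are assumptions chosen to show the range.

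**Step 1. Truncation, constant hazard, discharge unrelated to risk.** Let the death hazard be h per day and the mean time to discharge m days (exponential). Then P(death in hospital) = h / (h + 1/m). Take h = 0.005, so that 30-day mortality is 1 − exp(−0.15) = 13.9%.
- m = 8: 0.005 / (0.005 + 0.1250) = 3.85%
- m = 7.2 (10% shorter): 0.005 / (0.005 + 0.1389) = 3.47%
- Ratio 0.903, a relative fall of just under 10% with survival unchanged.

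**Step 2. Other shapes.** The probability is the integral of hazard × survival × P(still in hospital). Discharge time is gamma (shape 2, mean 8 days before ABF) and 30-day mortality is 5% to 15%, unchanged by the policy. Rate ratios, in-hospital, after versus before:

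| Reduction in stay | Constant hazard | Front-loaded hazard (5-day decay) |
|---|---|---|
| 5% | 0.95 | 0.98 |
| 10% | 0.90 | 0.96 |
| 20% | 0.80–0.81 | 0.91 |

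**Step 3. Risk-selective discharge.** Suppose only low-risk patients leave earlier. Example: 20% of patients are high risk, overall 30-day mortality is 13% and low-risk mortality 3%. High-risk mortality is then (0.13 − 0.8 × 0.03) / 0.2 = 53%.
- Hazards: −ln(0.97)/30 = 0.00102 (low risk) and −ln(0.47)/30 = 0.0252 (high risk).
- Before, m = 8 for all: 0.8 × 0.81% + 0.2 × 16.8% = 4.00%.
- After, overall mean 7.2, so low-risk mean 8 − 0.8/0.8 = 7.0: 0.8 × 0.71% + 0.2 × 16.8% = 3.92%.
- Relative fall about 2%, against 8.7% in the same population if every stay shortens alike.

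Varying the high-risk share (15% to 30%) and overall 30-day mortality (13% to 15%), with low-risk mortality of 2% to 5%, gives falls of about 1% to 4%.

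**Step 4. Muted harm.** Let true 30-day mortality rise from 10% to 11% (ratio 1.10) while stays shorten by 10%, under the Step 2 model. The in-hospital ratio is 0.996 with a constant hazard and 1.056 with a front-loaded one. The harm disappears in the first case and is roughly halved in the second.

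**Step 5. Patient mix.** If volume grows by a fraction g and the added cases carry r times the average mortality, the unadjusted rate ratio is (1 + g·r)/(1 + g). For g = 0.10:
- r = 0.5: 1.05/1.10 = 0.955
- r = 1: 1.10/1.10 = 1.00
- r = 1.5: 1.15/1.10 = 1.045

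The bias can go either way.

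**Step 6. The same truncation with a fixed window.** Death within 30 days of admission, wherever it occurs, has a ratio of 1.00 in Steps 1 to 3, because true 30-day mortality is held constant there.

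**The case against.** - *The adjustment may be there.* The mortality equation is not visible in the text available, the covariate vector is described by what it includes and not as a closed list, and adjustment is promised twice elsewhere. This stands. A reader might infer that mortality will be modelled with no risk adjustment; the article does not support that. It supports only that the Design and Analysis sections do not match, and that the promise concerns hospitals and not periods.
- *Hypothesis 1.1 does not predict lighter cases.* This stands too. A reader might infer that extra volume means lower-risk patients, so that both problems push towards apparent improvement. The hypothesis speaks only of more case-mix-adjusted volume, and Step 5 shows that added high-risk cases would raise the rate.
- *Table 1 says little about the mortality conditions.* Only congestive heart failure and hip replacement, two of the ten Table 2 conditions, are in Table 1, with expected responses of some and unknown. No shortening is quantified for the others. This limits how far the size can be generalised. Hypothesis 1.1 and the payment incentive are, however, stated for hospitals in general.
- *Discharge is not blind to risk.* Correct, and Step 3 shows that the effect can shrink to 1% to 4%. It does not vanish.
- *Other outcomes watch for early-discharge harm.* Readmissions within 30 days, readmissions from home care and surgical adverse events are planned, and Hypothesis 1.2 is undirected. They make it unlikely that one endpoint decides the question. None of them counts a patient who dies after discharge without returning.

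**Conclusion.** The concern holds in a limited form. In-hospital deaths per separation are sensitive to the shortening of stays that the study itself predicts, so a post-ABF change in this rate cannot by itself be read as a change in quality. On assumed inputs, a 10% shorter stay produces a spurious fall of about 4% to 10% if discharge is unrelated to risk, and about 1% to 4% if mainly low-risk patients leave earlier. These figures depend on when deaths occur and who is discharged sooner, neither of which the article gives.

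It would go too far to conclude that the study is bound to find no loss of quality: truncation may be small, harm may still show (1.056 in the front-loaded example), and a change in mix may push the rate up. The mismatch between the adjustment promised in the Design section and the model described in the Analysis section is a matter for reconciliation, with a bias of unknown direction.

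**What to change.** 1. **Outcome.** Make death within 30 days of admission, wherever it occurs, the main mortality outcome, using the registry link already planned; request the date of death if the extract lacks it. Keep in-hospital death as a secondary outcome. If no death date can be obtained, count deaths within 30 days of admission in any linked hospital stay, and state that deaths at home are still missed, so that this fallback reduces the truncation without removing it.
2. **Adjustment.** Reconcile the Design and Analysis sections by stating that patient risk (age, sex and ACG based on pre-admission data) enters the mortality model over time. Either patient-level covariates or an offset of expected deaths, from a model fitted on pre-ABF months only, would do.

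The two changes are both needed: the first deals with truncation and not with mix, the second with mix and not with truncation. The cost is one additional patient-level model and possibly one more field in the data request. ACG, age group and the registry link are already in the planned data.

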#### Information Base for Supporting ABF

The success of ABF is critically linked to the ability to measure 'weighted' hospital output accurately. Methods for characterizing hospital output according to the patients' mix of clinical conditions and interventions have become common and are known as case mix adjustments. The most popular method is diagnosis related groups, or DRGs [20], though variants of DRG have been developed, each customized to address local policy and health delivery characteristics and objectives [21,22]. In Canada, all acute inpatient discharge data submitted to the Canadian Institute for Health Information's (CIHI) Discharge Abstract Database (DAD) are case-mix-adjusted using their Case Mix Group (CMG+) methodology [23]. Case mix adjustment is important since it weights hospital discharges according to their expected relative use of resources (and therefore cost). Each CMG+'s expected relative cost is represented by a resource intensity weight (RIW). As the length of stay has no bearing on the RIW value assigned (with minor exceptions for patients with exceptionally long lengths of stay), the incentive is to shorten lengths of stay in order to keep actual costs below the RIW-based case-specific relative amounts.

The veracity of weighting hospital output by RIW is contingent on accurately reported clinical data. CIHI's clinical chart re-abstractions have shown that Canadian hospitals have modified their clinical coding behaviour to maximize RIWs even in the absence of direct financial incentives to do so [18,19]. This behavior introduces an additional challenge to our study and requires us to be able to differentiate actual changes in activity mix as a result of the changing financial incentives from apparent changes in activity mix that are merely shifts in coding practices.

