Using hospital data for all three categories of indicators, we will measure the association between rates of acute hospital readmissions and ABF. We will look for evidence of a change in 30 day hospital readmission rates for all causes, acute myocardial infarction (AMI) and prostatectomy discharges. Risk adjusted AMI readmission rate has been linked to the types of drugs prescribed at discharge, post-discharge therapies and the quality of follow-up care, whereas prostatectomy readmission rates provide one measure of follow up care [31,32]. These indicators are often used to signal too-early discharge. We will use ICD-10-CA diagnosis and Canadian Classification of Health Interventions (CCI) procedure codes to identify patients.

We will calculate indicators of system level effects on access: the rate of admissions from emergency department and the risk-adjusted rate of hip fracture in patients aged 65 and older who underwent hip fracture surgery on the day of admission or the next day. Increases in hospitals' emergency department utilization are linked to (less) availability of out-of-hospital care while delayed hip fracture surgery has been associated with a lack of resources, physician unavailability and other issues related to access to care [31].

We will calculate rates of hospital admissions for two ambulatory sensitive conditions: dehydration [33] and diabetes mellitus [33]. We believe changes in these rates are important signals of care quality and potentially negative implications for quality of life [34]. We are selecting these two conditions due to their broad use plus our ability to derive these indicators from B.C.'s hospital separation data. We will use the ICD-10-CA diagnoses to identify these patients.

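### Surgical complications are counted only during the stay, so if ABF shortens post-operative stay the recorded rates fall for that reason alone; a 30-day companion rate would be a cheap improvement.

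*Protocol article*

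**What the plan says.** Under Design, Aim 1, the three surgical complications are defined as follows: "We will also calculate in-hospital event rates, representing unintended injuries or complications of care [30] per volume of surgical separations". Change in trend is then analysed. The source is the separation record: "These quality indicators are commonly applied and can be readily computed with B.C.'s hospital separation data". No post-procedure follow-up window is given for them.

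On length of stay, the section Information Base for Supporting ABF says "the incentive is to shorten lengths of stay in order to keep actual costs below the RIW-based case-specific relative amounts", and Hypothesis 1.1 reads "Lengths of stay will decrease and case mix adjusted volume of patients will increase from baseline levels". The Design section qualifies this: "For each stratum, the change in the average length of stay and number of discharges is expected to vary". Table 1 gives an unknown response for benign prostatic hypertrophy and for hip and knee replacement, and no response for appendectomy and leg fracture.

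On use of the results: "In-hospital quality and outcomes as a result of a shift to ABF will be monitored in B.C. and shared with the MoHS".

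On events after discharge, Aim 2 plans readmission rates: "We will look for evidence of a change in 30 day hospital readmission rates for all causes, acute myocardial infarction (AMI) and prostatectomy discharges". Data Resources and Variable Construction lists procedure date, diagnosis codes and admission from the ED for the Aim 2 dataset. It also attributes readmissions at other hospitals to the first stay, and plans to exclude diagnosis codes that are prone to changes in coding practice.

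**The concern.** A complication can enter these rates only while the patient is in hospital. The policy under study is expected, in general, to shorten that period. If post-operative stay falls and some complications arise after the earlier discharge, they drop out of the numerator while the denominator (surgical separations) keeps the patient. A fall in the recorded rate could then be read as better safety, or a real rise could look smaller than it is.

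The other model terms do not separate the two. Hospital effects, the time trend and risk adjustment leave the window problem in place, because the window would change with the policy. The change would load onto the level term θ and the trend term τ, which are the parameters of interest. Since the results go to the Ministry, how a fall is interpreted matters.

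**Working it through.** The article gives no post-operative stay, event rate or event timing for these outcomes, so there is no figure to reproduce and every input below is an assumption.

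**Inputs assumed.** Post-operative stay L falls from 5 to 4.5 days. True complication risk is unchanged. Time from procedure to event follows one of three patterns: exponential with mean m = 3 days, exponential with m = 10 days, or a flat hazard over 30 days.

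**Share of events recorded by day L.** F(L) = 1 − exp(−L/m), or L/30 for the flat hazard.

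| Timing | F(5) | F(4.5) | F(30) | Ratio F(4.5)/F(5) | Recorded fall |
|---|---|---|---|---|---|
| m = 3 | 0.8111 | 0.7769 | 1.0000 | 0.9578 | 4.2% |
| m = 10 | 0.3935 | 0.3624 | 0.9502 | 0.9210 | 7.9% |
| Flat | 0.1667 | 0.1500 | 1.0000 | 0.9000 | 10.0% |

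**Weaker response.** If only half of patients go home earlier, or the lost half-day carries half the average risk, the fall is 0.5 × (1 − ratio): 2.1%, 4.0%, 5.0%. If post-operative stay is unchanged, it is 0%.

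**Absolute size.** At an assumed 3 true events per 100 surgical separations, the displaced events are 3 × [F(5) − F(4.5)] = 0.103, 0.093 and 0.050 per 100.

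**Opposing channel: coding.** The article notes that "Canadian hospitals have modified their clinical coding behaviour to maximize RIWs even in the absence of direct financial incentives to do so". A rise in complication coding of 1/ratio − 1 = 4.4%, 8.6% or 11.1% would cancel the fall exactly. With 10% more coding, 1.10 × ratio − 1 gives +5.4%, +1.3% or −1.0%. The net sign is therefore unknown.

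**Second check, by simulation.** Post-operative stay was gamma distributed (shape 2), and event times were exponential truncated at 30 days, with medians of 5, 8 and 12 days. With true risk unchanged, the recorded rate ratios were:

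| Mean stay, days | Median 5 | Median 8 | Median 12 |
|---|---|---|---|
| 7 to 6.3 | 0.94 | 0.93 | 0.91 |
| 7 to 5 | 0.82 | 0.78 | 0.74 |

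With stay falling from 7 to 5 days, a true 20% rise would be recorded as −2%, −6% or −11%. All simulated scenarios had shorter stay and no coding change, so they confirm the mechanism and not the net effect.

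**What a 30-day rate would do.** Let s be the share of post-discharge events counted on a readmission. The rate ratio is [F(4.5) + s(F(30) − F(4.5))] / [F(5) + s(F(30) − F(5))].

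| s | m = 3 | m = 10 | Flat |
|---|---|---|---|
| 0.5 | −1.9% | −2.3% | −1.4% |
| 0.8 | −0.7% | −0.7% | −0.4% |
| 1 | 0% | 0% | 0% |

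**Limit of that rate.** The table holds s constant. If ABF moved s from 0.50 to 0.55, the ratios would be:
- m = 3: 0.8996/0.9055 = 0.993
- m = 10: 0.6857/0.6718 = 1.021
- Flat: 0.6175/0.5833 = 1.059

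In two of the three cases that is a spurious rise with true risk unchanged. The companion rate is less exposed to the length of stay, but it is exposed to readmission practice.

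**The case against.** The strongest case against runs as follows. Hypothesis 1.2 concerns in-hospital quality and Aim 1 concerns changes internal to the hospital, so in-hospital rates measure what they are meant to measure. The hypothesis has no direction, and nowhere does the article say that a fall would be called a safety gain. Aim 2 already follows patients after discharge through all-cause readmission, readmission from home care and 30-day physician payments, and length of stay is itself modelled. Table 1 does not predict shorter stay for its listed surgical conditions, and the absolute displacement in the illustration is small.

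Much of this stands. It rules out several stronger readings that a reader might infer:

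- *ABF will make these rates fall.* This is not supported. Hypothesis 1.1 is general, Table 1 is unknown or nil for the listed surgical conditions, and coding may push the other way.
- *The in-hospital rates are the wrong indicators.* This is not supported. They are in common use and fit the stated aim.
- *Harm after discharge goes unmeasured.* This is not supported. All-cause readmission would register displaced complications that return to hospital within 30 days. What it cannot show is whether sepsis, thrombo-embolism or return to the OR has changed.
- *The Aim 1 data cannot support a fixed window because its variable list has no procedure date.* That list also omits sex and CCI codes, which the planned analyses need. It is evidently not exhaustive, so an absence from it proves little.

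What the objection does not remove is the narrow point. An unknown response is not an expected absence of response, the denominator is surgical separations and not the Table 1 conditions, and the in-hospital rate alone cannot tell fewer complications from a shorter time in which to see them.

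**Conclusion.** The point holds in conditional form, as a cheap improvement and not as an error in the plan. If post-operative stay shortens under ABF and some complications arise in the lost time, that mechanism alone lowers the three recorded rates or attenuates a true rise.

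The article does not allow the size to be derived. On assumed inputs with half a day lost from five, it is 4.2% to 10.0% in relative terms, or about 0.05 to 0.10 events per 100 surgical separations at an assumed 3 true events per 100. It is half the relative figure if the response is half as strong, and zero if stay does not change. Fuller coding could cancel or reverse it, so no net direction should be claimed.

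**What to change.** Keep the in-hospital rates as the standard indicators. For each of the three events separately, add a companion rate per index surgical separation:

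- Count the event if it is coded on the index stay, or on any acute readmission, at any hospital, with an admission date within 30 days of the index procedure date. The window is set by readmission date because the listed variables include no date for the complication itself.
- Attribute the event to the index hospital.
- Exclude planned or staged returns by a procedure list. Do not use admission from the ED as the filter, because Hypothesis 2.1 expects ABF to change it.
- Apply the planned coding exclusions to both rates, since a fixed window does not remove coding change.

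Estimate θ and τ for both rates and report them side by side with the length-of-stay and all-cause readmission results. Treat the companion rate as a sensitivity measure and not as the arbiter. State in advance that a fall in the in-hospital rate alone will not be interpreted as a safety gain.

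The cost is small, because the Aim 2 dataset already plans procedure dates, diagnosis codes and cross-hospital attribution. There are downsides. The measure needs the Aim 2 linkage and a list of planned procedures, and it departs from the standard indicator definition. Its capture may shift if readmission thresholds change under ABF, and it misses complications treated wholly outside hospital.
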